### Secondary outcome measures

Secondary outcomes include changes in patients' BP control, satisfaction with and willingness to pay for the service and economic benefits.

## Methods/Design

### Study Design

The HAPPY trial is a multi-centre prospective randomised controlled trial (RCT).

### Study Setting

Community pharmacies included in the trial come from metropolitan, regional and remote areas in three states of Australia (Victoria, Western Australia and Tasmania), proportionally stratified according to Pharmacy Access/Remoteness Index of Australia (PhARIA) [19] categories. (PhARIA provides a comprehensive, standardised measurement of the physical and professional remoteness of pharmacies throughout Australia, for use in the determination of rural and remote pharmacy allowances. The concept of remoteness was based on the road distance people have to travel to reach a range of services.) The pharmacies are located in a range of physical locations such as shopping strips, shopping malls, within medical centres and stand alone.

### Pharmacy Eligibility Criteria

Pharmacies that met all the following criteria were eligible to participate in the HAPPY trial:

• use the pharmacy dispensing program 'FRED Dispense^®^';

• agree to install a software application (MedeMine CVD) to identify patients who are using or have used antihypertensive medicines in the previous six months;

• have at least 40 patients who are currently using or have used antihypertensive medicines in the previous six months;

• have a private counselling area within the pharmacy where one-on-one consultation with a patient will be shielded from the public eye and ear;

• willingness and ability to attend project training either face-to-face or online;

• have time within the working week to allocate about one uninterrupted hour per patient to collect the baseline data; and

• able to follow-up participants for at least six months from baseline.

### Recruitment of pharmacies

Contact information for pharmacies was obtained from the telephone directory/Internet. Pharmacies in each of the PhARIA categories in each state were contacted by telephone and informed about the project. An explanatory statement and consent form was sent to all eligible pharmacies, if the pharmacist expressed interest. Upon receipt of the signed consent form, pharmacies were formally included in the study.

### Cluster randomisation

In each state, pharmacies were randomised to either Pharmacist Care Group (PCG) or Usual Care Group (UCG) according to the PhARIA. Randomisation was carried out at the pharmacy level to avoid the contamination likely to result from the same pharmacy recruiting and following up both intervention and control group patients. Randomisation was carried out at a central location using the sealed opaque envelope technique. To check for any 'Hawthorne effect' [20,21] in the UCG due to the effect of data collection, a third group of patients (Hidden Control Group - HCG) who are taking or have taken antihypertensives in the previous six months (but not included as participants in the UCG) will also be identified.

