**Methods/Design:**

The HAPPY trial is a multi-centre prospective randomised controlled trial. Fifty-six pharmacies have been recruited from three Australian states. To identify potential patients, a software application (MedeMine CVD) extracted data from a community pharmacy dispensing software system (FRED Dispense^®^). The pharmacies have been randomised to either 'Pharmacist Care Group' (PCG) or 'Usual Care Group' (UCG). To check for 'Hawthorne effect' in the UCG, a third group of patients 'Hidden Control Group' (HCG) will be identified in the UCG pharmacies, which will be made known to the pharmacists at the end of six months. Each study group requires 182 patients. Data will be collected at baseline, three and six months in the PCG and at baseline and six months in the UCG. Changes in patient adherence and persistence at the end of six months will be measured using the self-reported Morisky score, the Tool for Adherence Behaviour Screening and medication refill data.

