### Sample size

Australian, European and North American studies have estimated that around 50% of patients initiating an antihypertensive medication discontinue their medication (become nonpersistent) within twelve months [22]. To demonstrate a 15% difference in adherence between the control and intervention groups at six months (e.g. 50% in the UCG versus 65% in the PCG) with 80% power and a two-sided p-value of 0.05, 182 patients are required per study group. To allow for potential drop-outs (approximately 25% over six months) 225 patients need to be recruited per group; i.e. a total of 450 patients at baseline.

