### Data analysis

Participant characteristics in the UCG and PCG will be compared at baseline. Paired t-tests and/or Wilcoxon Signed Rank test will be used to compare changes in total scores on the Morisky scale, TABS and MedsIndex between the PCG and the UCG at baseline and six months. MedsIndex scores will be compared using paired t-tests and/or Wilcoxon Signed Rank test in the UCG and the HCG at six months.

Baseline data will be used to identify factors associated with suboptimal adherence in the whole study population. Significant factors in univariate analysis (chi-square, Mann-Whitney U test and Student's t-test) will be further tested in multivariate analysis (linear regression) to identify independent predictors of nonadherence/nonpersistence in the study population. To adjust for cluster randomisation, a pharmacy variable will also be included in the multivariate models.

An economic evaluation will also be carried out and will be reported elsewhere.

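### Pharmacies were randomised by state and PhARIA category, but the stated PCG-UCG comparison includes neither factor; a cluster-aware between-arm model should carry both

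*Protocol article*

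**What the plan says.** The unit of allocation is the pharmacy: "Randomisation was carried out at the pharmacy level to avoid the contamination" (Cluster randomisation). The same section gives the allocation factors: "In each state, pharmacies were randomised to either Pharmacist Care Group (PCG) or Usual Care Group (UCG) according to the PhARIA". The abstract gives the number of clusters: "Fifty-six pharmacies have been recruited from three Australian states".

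The Data analysis section sets the comparison of the two arms on the primary adherence scores: "Paired t-tests and/or Wilcoxon Signed Rank test will be used to compare changes in total scores on the Morisky scale, TABS and MedsIndex". State and PhARIA do not appear there.

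It names one adjustment: "To adjust for cluster randomisation, a pharmacy variable will also be included in the multivariate models". The paragraph containing that sentence opens with its purpose: "Baseline data will be used to identify factors associated with suboptimal adherence in the whole study population". The models therefore search for predictors of nonadherence and do not estimate the effect of the intervention.

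**The concern.** Allocating within strata balances the arms on the stratum factors, so differences between strata drop out of the arm comparison. If the analysis does not know about the strata, those differences stay in its residual variance. The reported standard error is then larger than the true one, confidence intervals are too wide and power is lost. With 56 clusters there is little precision to spare.

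The article names its tests, and the named tests cannot carry state or PhARIA. Carrying the pharmacy variable over to the arm comparison would not solve this. As a fixed effect it would be aliased with arm, because each pharmacy is wholly PCG or wholly UCG. As a random effect on its own it would leave the stratum variance in the error term.

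**Working it through.** **The plan's own figure.** For "e.g. 50% in the UCG versus 65% in the PCG" at 80% power and two-sided 0.05, the pooled two-proportion formula gives 169.3 per group, and 182.4 with continuity correction. The stated 182 is reproduced. It uses neither strata nor clustering, so this point changes no stated sample size.

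**Inputs.**
- From the article: 182 analysed patients per group and 56 pharmacies, so m = 2 × 182 / 56 = 6.5 analysed patients per pharmacy.
- Assumed, because the article does not give them: equal pharmacy sizes, ICC of 0.02 to 0.10, and a share R² of between-pharmacy variance explained by state and PhARIA of 10% to 50%.

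**A. Clustering handled, strata left out.**
- Between-pharmacy share of the variance of a pharmacy mean: s = ICC / (ICC + (1 − ICC)/m). At ICC 0.05, s = 0.05 / (0.05 + 0.95/6.5) = 0.255.
- Reported SE / true SE = 1/√(1 − s·R²). At R² = 0.3 this is 1/√(1 − 0.0765) = 1.041.
- Type I error = 2·P(Z > 1.96 × ratio).
- Power, where the analysis with strata would have 80%, is approximately Φ(2.80 − 1.96 × ratio).

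**B. Patient-level between-arm test, both pharmacy and strata ignored.** This stands in for the stated tests, because a paired or signed-rank test does not produce a standard error for the difference between two independent arms.
- True variance / reported variance: V = (1 − ICC) + m·ICC·(1 − R²) = 1 + (m − 1)·ICC − R²·m·ICC. At ICC 0.05 and R² = 0.3, V = 1 + 0.275 − 0.0975 = 1.1775.
- The reported SE is too small by 1 − 1/√V. Type I error = 2·P(Z > 1.96/√V).

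| ICC | R² | A: SE ratio | A: type I | A: power | B: V | B: SE too small by | B: type I |
|---|---|---|---|---|---|---|---|
| 0.02 | 10% | 1.006 | 4.9% | 79.7% | 1.097 | 4.5% | 6.1% |
| 0.02 | 50% | 1.031 | 4.3% | 78.3% | 1.045 | 2.2% | 5.5% |
| 0.05 | 30% | 1.041 | 4.1% | 77.7% | 1.178 | 7.8% | 7.1% |
| 0.05 | 50% | 1.071 | 3.6% | 75.9% | 1.113 | 5.2% | 6.3% |
| 0.10 | 10% | 1.022 | 4.5% | 78.8% | 1.485 | 17.9% | 10.8% |
| 0.10 | 50% | 1.125 | 2.7% | 72.5% | 1.225 | 9.6% | 7.7% |

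With R² = 0 the ratio in A is exactly 1. In B, V falls below 1 only when R² exceeds (m − 1)/m = 5.5/6.5, about 0.85.

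**Check by simulation.** The set-up was 56 pharmacies, 6 or 7 patients each, total variance 1, effect 0.3 SD, and an assumed 7 strata of 8 pharmacies.
- Stratum variance 0 and residual pharmacy variance 0: cluster-level power 0.81 without strata and 0.81 with them.
- Stratum variance 0.01 and residual 0.02 (ICC 0.03, R² one third): mean SE 0.1125 without strata and 0.1099 with them (ratio 1.02), power 0.756 and 0.764.
- Stratum variance 0.05 and residual 0.05 (ICC 0.10, R² 50%): mean SE 0.1285 and 0.1160 (ratio 1.11), type I error 0.030 and 0.047, power 0.634 and 0.711. In this scenario the patient-level test had type I error 0.077, against 7.7% in the table.

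**The case against.** The strongest objection is that the tests as written have the opposite problem. A reader might infer that, because the strata are ignored, the stated PCG-UCG tests are conservative. The article does not support that reading. Those tests ignore pharmacy as well, and over the whole assumed range a patient-level comparison has a standard error 2-18% too small and a type I error of 5.5-10.8%. The figures in part A describe a cluster-aware model without strata, which the article does not specify for the treatment comparison. This objection stands in full and confines the point to what remains after clustering is repaired.

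A second objection is that the loss is assumed. The article gives no ICC and no evidence that state or remoteness predicts adherence. It also analyses changes in scores, which already removes stable differences in level between strata, so an R² of 30-50% may be generous. This stands too: a loss of precision is possible but not shown.

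Third, the choice of stratification covariates is commonly left to an analysis plan. That carries less weight here, because the article names the tests and they have no place for the factors. Nor can a two-sample test be read into the plan: Student's t-test and Mann-Whitney are named only for univariate screening of baseline predictors.

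Finally, the Study Setting section's remark about PhARIA stratification describes which pharmacies were included, not how they were allocated. The point rests on the Cluster randomisation section alone.

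**Conclusion.** The mismatch is real and lies in a method that the article states: allocation was by state and PhARIA, and no stated treatment comparison includes either factor. It is a minor point, secondary to the neglect of clustering and to the use of paired tests for independent arms.

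Its size is conditional. Once clustering is respected, the loss is nil if the strata are not prognostic. Otherwise the standard error is about 1-12% too large, giving a conservative test and power of about 72-80% where the matched analysis would have 80%. This rests on 6.5 analysed patients per pharmacy, an ICC of 0.02-0.10 and 10-50% of between-pharmacy variance explained. The article supports only the first of these, and only as an average.

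**What to change.** Replace the stated PCG-UCG tests with a between-arm model of each six-month primary score. Give it a random pharmacy effect, and fixed effects for arm, baseline score, state and PhARIA category. Fix in advance a rule for pooling adjacent sparse PhARIA categories, for example where a category has fewer than two pharmacies per arm. This repairs the clustering and the unsuitable paired tests in the same step.

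No new data are needed, since both factors were used to allocate every pharmacy. The cost is a few degrees of freedom out of 56 clusters: two for the three states, plus one fewer than the number of PhARIA categories kept. The article does not state that number. In the simulation, seven strata reduced the residual degrees of freedom from 54 to 48 and cost no visible power when the strata were not prognostic.

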### Pharmacist Care Group (PCG)

The PCG participants receive a package of interventions from the pharmacist for enhancing their antihypertensive medication adherence, which includes:

• a home BP monitor (Omron^®^T9IT) with the capacity to store and download BP readings to be used for discussion at three- and six-month follow-ups;

• training by the pharmacist on self-monitoring of BP;

• motivational interviewing and education by the pharmacist to help patients improve their medication adherence and achieve target BP;

• pharmacist-initiated home medicines review (HMR), dose administration aid (DAA) and/or patient medication profile (PMP), where necessary;

• medication use review (MUR) to identify and resolve possible medication-related hypertension (e.g. due to non-steroidal anti-inflammatory drugs, cold preparations, complementary medicines, etc.);

• referral to a GP when needed (e.g. very high blood pressure); and

• refill reminders (by either SMS, telephone or mail) from their pharmacist at a chosen number of days before their antihypertensive medication dispensing is due.

HMRs http://www.medicareaustralia.gov.au/provider/pbs/fourth-agreement/hmr.jsp are designed to assist consumers living at home to maximise the benefits of their medication regimen and prevent medication-related problems. The review involves the consumer's general practitioner (GP) and preferred community pharmacy, and in some cases other relevant members of the healthcare team. The GP refers the consumer to the community pharmacy and an accredited pharmacist visits the consumer at home, reviews their medication regimen, and provides the GP with a report. The GP and consumer then agree on a medication management plan.

A DAA http://www.health.gov.au/internet/main/publishing.nsf/Content/ppsac-qa-daa is a device developed to assist patients in better managing their medicines by arranging their medicines into individual doses according to the prescribed dose schedule throughout the day. The aim of the DAA Program is to reduce medication-related hospitalisation and adverse events through improving medication management and adherence for people in the community.

A PMP http://www.health.gov.au/internet/main/publishing.nsf/Content/ppsac-qa-pmp is a comprehensive written summary of all regular medicines taken by a patient that assists them in understanding and managing their medicines by informing them how, when and why to take their medicines. The aim of the PMP Program is to reduce the risk of medication-related adverse events by assisting people to understand and manage their medications, including prescription, over-the-counter and complementary medicines.

A MUR http://www.psnc.org.uk/pages/murs_the_basics.html usually takes place in the pharmacy and it involves the pharmacist checking the patient's medication, making sure that the patient knows how and why they should be taking their medication, as well as identifying any problems. It provides the patient with an opportunity to ask questions and the pharmacist an opportunity to improve the patient's medication understanding and adherence, as well as being able to highlight problems and provide appropriate solutions.

### Usual Care Group (UCG)

UCG pharmacists will continue to offer routine care to their patients.

### Training for Pharmacists

Training was organised for all participating pharmacists in two modes, face-to-face and online. Materials and resources were made available as hard copy, online and on CDs, to provide flexible learning opportunities. Training comprised two phases:

### Phase I

Phase I training was delivered to all participating pharmacists and included the project overview, patient recruitment including the use of MedeMine CVD software to identify patients using antihypertensive medications, calculation of MedsIndex score, use of BP monitors and collection of baseline data.

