### Primary outcome measures

The primary outcomes of the HAPPY trial are changes in patient adherence and persistence at the end of six months. These will be measured subjectively using the self-reported Morisky scale [16] and the Tool for Adherence Behaviour Screening (TABS) [17] and objectively using the medication refill data (e.g. MedsIndex score [18]). The Morisky scale assesses both intentional and unintentional nonadherence and comprises four items. Responses for each item are scored 0 for 'yes' and 1 for 'no' (except for the item 'are you always careful in taking medicines?' where the score was reversed) and added together. A total score of zero represents good adherence and a score of one or more represents suboptimal adherence. The TABS is another self-reported adherence measure, which was originally developed in Australian patients using chronic medicines. It has two subscales - 'adherence' and 'nonadherence' - each comprising four items to be answered on a 5-point Likert-type scale ('never' - 1 to 'always' - 5). The total score for 'nonadherence' will be subtracted from that of 'adherence'; a differential of ≥15 will be regarded as good adherence and ≤14 will be regarded as suboptimal adherence. The TABS measures both intentional and unintentional deviations from recommended management and has been shown to have greater incremental validity than other self-reported adherence measures [17]. The MedsIndex gives each patient a score out of 100 for each of their long-term medications, which is calculated based on their refill history. Any score less than 100 suggests suboptimal adherence.

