### Data collection

### Baseline visit

During the baseline visit to the pharmacy, the pharmacist will measure the patient's BP using a digital BP monitor (average of two readings as per WHO MONICA [23] and EHRM [24] protocols - if these differ by more than 5 mmHg, a third reading will be taken and the average of the two closest readings will be recorded). Each pharmacy has been provided with a BP monitor. The MedsIndex score will be calculated for each antihypertensive medicine the patient uses. Adherence will be measured using self-report tools - the Morisky scale and the TABS. The Beliefs and Behaviour Questionnaire [17] will be used to assess patient experiences, attitudes and beliefs regarding their health and treatment and the 8-item short Assessment of Quality of Life (AQoL) [25] will be used to measure health-related quality of life. The pharmacist will also collect information on the patient's medications and their understanding of and ability to use these medications. The PCG will also receive the intervention described earlier.

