### Ethics

This project has been approved by the Human Research Ethics Committees of Monash University, Curtin University and The University of Melbourne, and the Human Research Ethics Network of Tasmania. All pharmacists and patient participants (in the UCG and PCG) provided written informed consent at the time of enrolment.

Approval to access dispensing data for the HCG was given on the basis that pharmacists have routine access to this data about their patients via the dispensing program and would use it in normal practice to routinely check their patient's history for actual or potential medication-related problems. The researchers will have access only to deidentified patient data.

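### The refill score, the one primary measure called objective, appears to be calculated at the visits by pharmacists who know their arm; the outcome value should be calculated centrally and masked

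*Protocol article*

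**What the plan says.** **Status of the measure.** The Primary outcome measures section has three instruments. Morisky and TABS are self-reported. Adherence and persistence are also to be measured "objectively using the medication refill data", with MedsIndex as the example. MedsIndex gives a score out of 100 for each long-term medicine, "which is calculated based on their refill history", and the section adds: "Any score less than 100 suggests suboptimal adherence".

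**Who is trained to produce it.** Phase I training went to all participating pharmacists and included "calculation of MedsIndex score, use of BP monitors and collection of baseline data".

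**When it is produced.** The Baseline visit section, which describes what happens at the pharmacy, states: "The MedsIndex score will be calculated for each antihypertensive medicine the patient uses". The Six-month visit section repeats the baseline measures in both randomised arms at a pharmacy visit.

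**What the pharmacist knows.** Randomisation is by pharmacy. PCG pharmacists were offered Phase II training before baseline data collection and deliver the intervention package. UCG pharmacists receive that training only after the six-month follow-up.

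**What data the researchers may hold.** MedeMine CVD extracts data from the dispensing system and creates a unique identification number for each participant. The Ethics section states: "The researchers will have access only to deidentified patient data".

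**The concern.** Every other adherence measure in this trial is self-reported to a pharmacist who knows the allocation. The refill score is the only primary measure that could act as an independent check on self-report. If the people who deliver the intervention also produce the score, that independence is weakened.

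The exposure is not symmetrical. A PCG pharmacist has spent six months trying to raise adherence; a UCG pharmacist has not. Any choice made while working out the score could lean in favour of the PCG. Two features of the article make such choices conceivable. The score covers the medicines a patient uses, while the inclusion criteria also admit people who only used an antihypertensive at some point in the last six months. And any value below 100 counts as suboptimal, so a small change in a score can change a patient's class.

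What is at stake is bias in the PCG versus UCG comparison on the measure that readers will trust most.

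**Working it through.** **Step 1. Does the article assign the calculation to pharmacists?**

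- Phase I: all pharmacists are trained to calculate MedsIndex.
- Baseline visit: the calculation is listed between the pharmacist's BP measurement and the self-report tools. The sentence is passive and names no calculator.
- Six-month visit: the same measures are repeated at the pharmacy.

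If a central routine produced the outcome value, there would be little reason to train every pharmacist to calculate it. Calculation by the pharmacist is therefore a strong inference, but an inference.

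**Step 2. Can that person be masked?** No. Allocation is by pharmacy, and the PCG pharmacist delivers the package.

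**Step 3. Does the text leave the pharmacist a scoring choice?** It states none. It says that the score comes from refill history and covers each antihypertensive used. The rules may stand in the cited tool or in the full protocol, neither of which is shown.

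**Step 4. The plan's own figure.** The Sample size section gives 50% versus 65%, 80% power, two-sided 0.05 and 182 per group.

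- Without continuity correction: n = [1.96·√(2·0.575·0.425) + 0.8416·√(0.5·0.5 + 0.65·0.35)]² / 0.15² = (1.3702 + 0.5816)² / 0.0225 = 169.3, so 170.
- With continuity correction: n = (169.3/4)·[1 + √(1 + 4/(169.3·0.15))]² = 182.4, which is 183 rounded up.

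The stated 182 is reproduced with the correction.

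**Step 5. Illustration of size.** The documents give no rate of arm-dependent scoring, so the shift *b* is assumed. Take 182 per group, a true adherent share of 50% in both arms, no clustering, and a PCG share recorded as 50% + *b*.

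- Standard error with no shift: √(2·0.5·0.5/182) = 0.0524.
- Rejection probability: Φ[(b − 1.96·SE₀)/SE₁] + Φ[(−b − 1.96·SE₀)/SE₁], where SE₀ uses the pooled share and SE₁ the two separate shares.
- For b = 0.05: SE₀ = √(2·0.525·0.475/182) = 0.05235 and SE₁ = √((0.25 + 0.2475)/182) = 0.05228. This gives Φ(−1.006) + Φ(−2.919) = 0.157 + 0.002 = 0.159.

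| Assumed shift in PCG share | Two-sided false-positive rate |
|---|---|
| 0 points | 5% |
| 2 points | 6.7% |
| 5 points | 15.9% |
| 10 points | 48.3% |

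A 5-point shift is one third of the 15-point difference the trial is sized for (5/15).

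**Step 6. Limits of the illustration.** It moves patients across a cut-off, whereas the Data analysis section compares total MedsIndex scores. The 50% and 65% are an example for adherence in general and are not tied to MedsIndex. The table shows how sensitive a comparison of this size is to a small systematic shift; it does not estimate the bias in this trial.

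**The case against.** The strongest reply is that a score computed from dispensing records is largely mechanical. No sentence gives the pharmacist discretion, the baseline sentence does not say who calculates, and a condensed article may leave the scoring rules and look-back period to the full protocol. All of this stands. It means that arm-dependent scoring cannot be asserted as fact, and that the absence of a stated window is not an error in this document. It does not remove the point that the procedure, as described, puts the calculation with unmasked staff when a masked route is available.

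Three stronger readings are tempting, and the documents do not support them.

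- **Contamination of the control arm.** A reader might infer that calculating the score breaks the promise that "UCG pharmacists will continue to offer routine care to their patients". But MedeMine CVD already preferentially identifies patients with suboptimal refill adherence in both arms, the Ethics section describes checking dispensing history as normal practice, and Morisky and TABS are completed at the same visit. The HCG is also the plan's own check for an effect of data collection in the UCG.
- **Different measurement routes for UCG and HCG.** A reader might infer this because HCG patients are hidden until the end of six months. A retrospective refill score needs no visit, and the text fits the same pharmacists using the same dispensing system at that point.
- **Dilution of the six-month change by pre-baseline refills.** This would require that the whole history is scored and that its length is known. The article states neither.

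A practical objection also stands in part: dispensing data alone cannot tell a medicine stopped by the prescriber from nonadherence, so some information collected at the visit is still needed.

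**Conclusion.** The point holds in limited form. Taken together, the Phase I, Baseline visit and Six-month visit sections imply that the only primary measure called objective is worked out by pharmacists who know their arm and who, in the PCG, delivered the intervention. The article describes no masked or central calculation.

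The conclusion rests on one inference, that the passive baseline sentence refers to the pharmacists trained for the task. The bias itself is a risk of the design and has not been demonstrated. Its size is unknown, and the rise from 5% to about 16% holds only under the assumed 5-point shift and the simplifications listed in the working. The case for a change rests less on that figure than on the fact that a less bias-prone method is available at little cost.

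**What to change.** Amend the Baseline visit and Six-month visit sections so that the outcome MedsIndex, at both time points, is calculated centrally by the researchers:

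- from the deidentified dispensing extract, linked by study identification number;
- with the arm label masked;
- with one fixed rule set applied alike to PCG, UCG and HCG.

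Pharmacists may still view a score for their own use, but that value is not the outcome. Because the score derives from recorded refills, the baseline value can also be calculated retrospectively, provided that the extract reaches back far enough. Completed baseline visits are then no obstacle.

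The cost is one extract per pharmacy (56 pharmacies) and one script. Documented prescriber-initiated stops or switches must be supplied as data and handled under a common rule. That input still comes from unmasked staff, so the change narrows the room for arm-dependent scoring without closing it.
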